**Fig. 3 Fig3:**
[figure not shown]
Power curves for different combinations of cluster autocorrelations (CACs) and intra-cluster correlations (ICCs). **A** Power curves assuming a reduction in the primary outcome of in-hospital mortality within 30 days from 20% under standard care to 15% after ATLS® training. **B** Power curves assuming a reduction in the primary outcome from 10% under standard care to 7.5% after ATLS® training. Under this scenario, we would need to increase the sample size per month to approximately 30 observations to achieve 90% power under most combinations of CACs and ICCs

### Nested staircase design

The secondary outcomes that will be measured using the nested staircase design are adherence to ATLS® principles during initial patient resuscitation, quality of life, and disability. We will not include any multiplicity adjustment as analyses of these outcomes are intended to be hypothesis driving only. The expected effects of the intervention on each of these outcomes include an improvement in adherence from 50% during standard care to 70% after training [42], an increase in EQ5D5L health status from 70 during care to 75 after training [43], and a decrease in disability from a baseline value of 25 during standard care to 22.5 after training [44]. For quality of life and disability, these effects correspond to standardised effect sizes, expressed as Cohen’s *d* of 0.5. With a total of 30 clusters, six per sequence, for a discrete time decay correlation structure, with ICCs of 0.01 to 0.15 and a CAC of 0.8, there is > 80% power to detect these effects by including four patients in each cluster in each period. To account for loss to follow-up, we will include at least six patients per cluster per month, sampled as described under Sequence generation {16a} below.

## Recruitment {15}

Participant data collection will include all participants who meet the eligibility criteria. These participants will be adult trauma patients who present to the emergency department of a participating hospital. Participants cannot opt out of the intervention because it is implemented at the cluster level and involves training physicians in ATLS®, and it is unreasonable to expect these physicians to temporarily disregard their training. However, patient participants can choose to withdraw their consent for the collection of non-routinely recorded data at any time before the final analysis. If patients withdraw their consent for the data collection, no further data collection will be performed, including follow-up data. Participants can also choose to remove the previously collected data in the trial at any time before the final analysis of the data. Withdrawal of consent or removal of data from the trial will not affect patients’ care in any way. If a participant withdraws consent, follow-up will be performed according to the participating hospital’s routine. We will document and report the total numbers of withdrawals (by cluster and period).

## Assignment of interventions: allocation

### Sequence generation {16a}

Clusters will be assigned to batches as they are found to be eligible and receive ethical approval. We will randomise the clusters within each batch to the different intervention implementation sequences within that batch [37]. The randomisation will be balanced within each batch on cluster size, defined as the monthly volume of eligible patient participants, using covariate constrained randomisation. Cluster sizes are expected to vary from 12 and to 20 patients per month, based on our previous experience.

Patients included for measurement of the secondary outcomes adherence to ATLS® principles, quality of life, and disability under the nested staircase design will constitute a random subset of patients included during the staircase months. The random subset will be selected using simple random sampling at the shift level, meaning that the timing of the clinical research coordinator’s shift will be randomised to cover approximately 8 h during the morning, afternoon, or night shift. ATLS® adherence will be recorded for all patients included during these shifts. Quality of life and disability will be recorded for all patients included during the days of the randomised shifts. In each hospital, the number of shifts that will be randomised will be determined by the volume of patients included during the months preceding the staircase months.

### Concealment mechanism {16b}

The randomisation will be concealed for as long as it is logistically possible, considering that arrangements for sending physicians to ATLS® training must be made in advance.

### Implementation {16c}

The allocation sequence is generated by JM. Participants are included by clinical research coordinators at each participating site. The time point when the intervention is implemented is determined by the randomised intervention sequence, and participants included after this time point are considered exposed to the intervention.

## Assignment of interventions: blinding

### Who will be blinded {17a}

It is not possible to blind trial participants or care providers in this stepped-wedge trial. We will not blind outcome assessors nor data analysts because of how the intervention is randomised by time. Instead, to protect against issues related to an unblinded analysis of the data, a full statistical analysis plan—including example code and descriptions of all sensitivity analyses—will be published online prior to the trial statistician receiving any data.

### Procedure for unblinding if needed {17b}

Not applicable as the trial is not blinded.

## Data collection and management

### Plans for assessment and collection of outcomes {18a}

The outcomes will be assessed and collected as described in Table 1. Outcome recording will be verified for a sample of observations through remote and on-site monitoring of source data by the coordinating centre the George Institute for Global Health in India. The source data of all patients who die in-hospital are reviewed. Data collection will be performed via a paper-based case record form (CRF), which will then be transferred to an electronic CRF (eCRF) on REDCap [45, 46]. The site investigators will keep source documents for each patient participant in the trial. A document describing what has been classified as source data in the trial (source data reference document) will be included in the Investigator Site File (ISF). Data will be registered, managed, and stored in a manner that enables correct reporting, interpretation, and verification. All documentation will be stored securely and retained according to regulatory requirements. The complete Trial Master File, as well as source documents, will be archived for at least 10 years after the trial is completed. Source data in the medical records system are stored and archived in accordance with Indian national regulations. The metadata will be publicly accessible via a persistent DOI, and anonymized data will be released upon project completion.

### Plans to promote participant retention and complete follow-up {18b}

The primary outcome is extracted from medical records and is known to be missing to a negligible extent. To promote complete telephone follow-up following discharge, we collect multiple phone numbers for each participant. For outcomes collected through telephone follow-up, at least three calls are attempted. Depending on the response, a subsequent call to complete the follow-up may be scheduled. In cases where no contact can be established despite repeated attempts, the participant is classified as lost to follow-up.

## Data management {19}

Data entry will be performed in REDCap. The George Institute for Global Health India will be the coordinating center in India. It will be the responsibility of the George Institute to train site investigators and site staff before the trial about the documentation requirements and data collection procedures. Data management will be performed through ongoing quality metrics assessment, review of missing data and outliers, and documentation in the investigator site file. Study-related documents will be stored securely and retained according to regulatory requirements. Data management will strictly follow ICH GCP principles and Indian regulations. Access to trial-related documentation, such as patient participants’ medical records, CRFs, other source data and other trial documentation, will be provided for monitoring and auditing purposes. Access will also be granted in the context of regulatory inspections. Pseudonymised data will be transferred to secure servers at Karolinska Institutet for analysis.

## Confidentiality {27}

All the data will be handled according to the Indian Council of Medical Research’s guidelines and the standard operating procedures of the George Institute for Global Health India on data security and protection. Trial data will be stored and shared via the eCRF throughout the trial. The eCRF will be accessible via two-factor authentication, and the data will be held on a secure server. All investigators and trial site staff involved in this trial must comply with the requirements of the ICMR guidelines on data security and protection.

### Plans for collection, laboratory evaluation and storage of biological specimens for genetic or molecular analysis in this trial/future use {33}

No biological specimens will be collected in this trial.

## Statistical methods

### Statistical methods for primary and secondary outcomes {20a}

The primary analysis set will include all observations within clusters with available data and irrespective of the receipt of the intervention. Clusters and observations within clusters will be considered exposed to the intervention after the date at which the cluster was scheduled for transition. All the data will be included except the transition phases.

We will not adjust for multiplicity of analyses because none of the secondary outcomes will be singularly more important. However, all secondary outcomes will be interpreted with due consideration for the way all are affected by the intervention without undue emphasis on a single outcome that might be statistically significant when all others appear to have remained unchanged.

We have several requirements for the analysis model. First, all analyses will consider the clustered nature of the design. Second, as the trial has only 30 clusters, it will be essential for the model to allow for correction due to the small number of clusters. Third, as the design is a stepped-wedge study, we will adjust for temporal confounding following standard approaches with categorical effects for the period of the study (1 month) [47, 48].

In the case of binary outcomes, the primary estimand will be the odds ratio obtained from a mixed effects binomial regression with a logit link. We will also apply a binomial model with an identity link to estimate the risk difference. These models will be fitted using residual pseudo-likelihood estimation based on linearisation with subject-specific expansion (RSPL). If the binomial model with the identity link does not converge then only an odds ratio will be reported.

We will include fixed effects for period and a fixed effect for intervention exposure. The primary analysis will allow for clustering as a random cluster and random cluster by period effect. To correct potential inflation of the type I error rate due to the small number of clusters, a correction for a small number of clusters will be applied. Our primary method will be a Kenward-Roger correction [49], but this choice might be updated based on new methods work available closer to the end of patient inclusion, and may differ for the outcomes collected via the complete main stepped-wedge design and incomplete nested staircase designs.

We will use a two-sided significance level of 5% and estimate 95% confidence intervals.

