## Sample size {14}

### Main stepped wedge design and primary outcome

With 30 clusters across six batches and a total participant sample size of at least 4320, our study has ~ 90% power across different combinations of cluster autocorrelations (CACs) and intracluster correlations (ICCs) to detect a reduction in the primary outcome of in-hospital mortality within 30 days from 20% under standard care to 15% after ATLS® training (see Fig. 3A), meaning a 5% units absolute reduction [37]. This effect is a conservative estimate because our updated systematic review indicates a stronger effect. The reduction equals a risk ratio of 0.75, which would be clinically important and consistent with our pilot study and updated systematic review [19, 31]. We allow for the clustered design, incorporate the 1 month transition period, and assume: a discrete time decay correlation structure, an ICC of 0.02 (but consider sensitivity across the 0.01–0.05 range) and a CAC of 0.9 (but consider sensitivity across the 0.8–1.0 range), based on our pilot study and current guidance [38–41]. We included the CAC to allow for variation in clustering over time. We assume that each cluster will contribute approximately 12 observations per month to the analysis, but allow for substantial variations in cluster sizes, on the basis of our previous work. We also estimated the sample size required to detect a reduction in the primary outcome from 10% to 7.5%, which would require at least 30 observations per period and cluster (Fig. 3B).

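### If the identity-link model does not converge, the plan reports only an odds ratio and gives up the period-adjusted risk difference, which could be standardised from the primary logit model

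*Protocol article*

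**What the plan says.** All of this is in the protocol article.

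- **Primary estimand.** For binary outcomes, section {20a} says "the primary estimand will be the odds ratio obtained from a mixed effects binomial regression with a logit link".
- **Risk difference.** The same paragraph adds one route to an absolute effect: "We will also apply a binomial model with an identity link to estimate the risk difference". Both models are fitted by residual pseudo-likelihood.
- **Fallback.** "If the binomial model with the identity link does not converge then only an odds ratio will be reported". No other section gives another route to a risk difference.
- **Model terms.** Section {20a} specifies categorical monthly period effects, an intervention effect, and random cluster and cluster-by-period effects. It also calls a correction for the small number of clusters essential and names Kenward-Roger as the primary method.
- **Target effect.** The sample-size section {14} uses "in-hospital mortality within 30 days from 20% under standard care to 15% after ATLS® training", which it glosses as "meaning a 5% units absolute reduction". It adds: "The reduction equals a risk ratio of 0.75". It also considers a fall from 10% to 7.5%.

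**The concern.** The target is described as an absolute difference and as a risk ratio, while the fallback leaves only an odds ratio. An odds ratio translates into an absolute effect only through the base risk, and the protocol is unsure enough of that risk to plan for both 20% and 10%.

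Raw percentages by condition do not fill the gap. In a stepped wedge, exposure is confounded with time, which is why the plan adjusts for period. Without a model-based risk difference, readers would have no period-adjusted absolute effect with a confidence interval.

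Whether that measure appears would then depend on convergence of the more fragile of the two models. The rule covers every binary outcome, including 24-hour mortality, which cannot have more events than 30-day all-cause mortality.

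**Working it through.** **1. The plan's own figure.** The inputs in section {14} are 30 clusters and "each cluster will contribute approximately 12 observations per month to the analysis". Each cluster includes patients for 13 months, of which 1 is the excluded transition month, leaving 12.

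30 × 12 × 12 = 4320, as stated.

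Power was checked by generalised least squares on cluster-period means, with discrete time decay, ICC 0.02, CAC 0.9, two-sided 5%, and month effects shared across batches that start every 7 months. The step months are in a figure that is not shown, so several layouts were tried. Power was 0.85 to 0.89, the best match being 0.891 with transitions in months 4, 6, 7, 8 and 10. This agrees with the stated figure of about 90%. With batch-specific month effects it falls to about 0.35 to 0.70, which is a separate matter.

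**2. The target as an odds ratio.**

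(0.15/0.85) / (0.20/0.80) = 0.1765 / 0.25 = 0.706.

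The cluster-conditional odds ratio giving the same marginal risks is 0.704, 0.701 and 0.694 at ICC 0.01, 0.02 and 0.05. The gap between conditional and marginal is therefore small.

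**3. What that odds ratio means at other base risks.** Intervention odds = 0.706 × p/(1 − p), converted back to a risk:

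| Standard-care risk | Intervention risk | Difference (points) |
|---|---|---|
| 10% | 7.3% | 2.7 |
| 15% | 11.1% | 3.9 |
| 20% | 15.0% | 5.0 |
| 25% | 19.0% | 6.0 |

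**4. Why the identity link may fail.**

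- Deaths per cluster-month are 12 × 0.20 = 2.4 under standard care and 12 × 0.15 = 1.8 under intervention.
- On the risk scale the between-cluster SD is about √(ICC × p(1 − p)). At p = 0.20 this is √(0.02 × 0.16) = 0.057 for ICC 0.02 and √(0.05 × 0.16) = 0.089 for ICC 0.05.
- A cluster two SDs below a 15% intervention risk then has 15 − 11.3 = 3.7% at ICC 0.02 and 15 − 17.9 = −2.9% at ICC 0.05, before any noise in the month effects. Fitted risks below zero are therefore a realistic prospect.
- The number of month effects is not fixed by the article. With calendar months and a batch every 7 months (13 months less the anticipated 6-month overlap), it is 13 + 5 × 7 = 48. With months since cluster start, it is 13 at most.

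**5. Simulation (illustrative).** Own pseudo-likelihood code, 60 data sets per row, both random effects included, fitted risks outside 0 to 1 counted as failure:

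| Period effects | Base mortality | Random-effect SD (logit) | Logit converged | Identity converged |
|---|---|---|---|---|
| Calendar month | 20% | 0.357 (ICC about 0.02) | 60/60 | 28/60 |
| Calendar month | 20% | 0.574 (ICC about 0.05) | 60/60 | 5/60 |
| Since cluster start | 20% | 0.33 | 60/60 | 55/60 |
| Since cluster start | 20% | 0.6 | 60/60 | 24/60 |
| Since cluster start | 10% | 0.45 | 60/60 | 21/60 |
| Since cluster start | 10% | 0.8 | 60/60 | 0/60 |

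At 10% mortality with calendar months, one logit fit also broke down, probably in a month without deaths; that scenario was not completed.

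**6. Is the alternative workable?** In the first row, the risk difference standardised from the logit fit averaged −0.051, with empirical SD 0.014 and mean delta-method SE 0.014. In the second row it averaged −0.055, with SD 0.014 and mean SE 0.016. I take this as evidence that the estimator can be computed and that its standard error is about right. With 60 data sets per row it is not a proof of unbiasedness.

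**The case against.** The best defence is that nothing primary is lost. The odds ratio is the declared primary estimand, the identity-link model is additional, and a stated fallback to the primary estimand is transparent. The trial is sized on two proportions, and an odds ratio of 0.706 is the same alternative on another scale. The trial will also observe its own standard-care mortality, from which a reader can work out an approximate absolute effect. All of this stands. It confines the point to a supplementary measure, but that approximation comes without a model-based interval.

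Four stronger readings are tempting, and the documents do not support them.

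- **The main result or the power is compromised.** It is not. Reporting the main result as an odds ratio follows from the choice of estimand, whether or not the identity model converges.
- **The logit model already contains the risk difference.** It gives a cluster-conditional odds ratio. A risk difference needs a further step that integrates over the random effects, and an interval method.
- **Failure is close to certain because there are 48 month effects.** The article does not say whether periods are calendar months, and the overlap is only anticipated. The Trial status section gives inclusion from late February 2025 to about November 2029, roughly 57 months, so 48 is an assumption. Under one 13-period setting the identity link converged in 55 of 60 data sets.
- **Readers will be misled because 0.706 looks like a 29% reduction where the target was 25%.** That requires taking the odds ratio for a risk ratio, and nothing in the protocol does so.

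An objection to the remedy also has force. A plain delta-method interval would drop the small-sample correction that the plan calls essential. A bootstrap within batches of five clusters, one per sequence, would omit or duplicate sequences. The remedy has to allow for this.

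The statistical analysis plan, which is not shown, could add another route. As written, however, the article's rule excludes one.

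**Conclusion.** The point holds as a minor to moderate one. Followed literally, the fallback can leave the trial without a period-adjusted risk difference and interval for a target that the protocol states in absolute terms. The same odds ratio spans 2.7 to 5.0 points across the two base rates considered. The primary estimand, test and power are unaffected.

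That the rule exists and what it would cost follow from the text and simple arithmetic. That failure is plausible rests on about 2 deaths per cluster-month, monthly categorical effects and two random effects. How likely it is cannot be fixed from the documents: it depends on the software, the convergence criterion, the period definition, the base mortality and the ICC.

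**What to change.** Replace the odds-ratio-only fallback in section {20a} with a prespecified risk difference and risk ratio from the primary logit mixed model, by marginal standardisation:

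1. Predict risks with all patients set to intervention and then to standard care, over the observed periods.
2. Integrate these predictions over the cluster and cluster-by-period random effects, then average.
3. Report the difference and the ratio with a delta-method interval that carries a small-sample correction for 30 clusters, for example a t reference distribution with stated degrees of freedom.

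This could be the planned absolute-effect estimator, with the identity-link model kept as a supporting analysis, or at least the fallback. The statistical analysis plan should also say whether periods are calendar months or months since cluster start.

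The cost is modest: some wording and code, no new data, and no change to the primary test. The interval on this scale is not directly Kenward-Roger, and the method still needs the primary logit model to converge. Section {17a} commits to publishing the analysis plan before the trial statistician receives any data, so the change can be made there.

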### Interim analyses {21b}

There will be one interim analysis after half of the batches have completed the trial. The interim analysis will be assessed by the joint Trial Steering and Data Monitoring Committee. The purposes of this interim analysis will be to assess the trial’s feasibility and recommend that the trial be stopped if it is not feasible (e.g. if hospitals fail to adhere to the randomisation schedule or if there are substantial missing data in outcomes), and to compare characteristics across intervention conditions to monitor for differential recruitment/ascertainment between the intervention and control groups. No efficacy stopping rule is planned because any estimates obtained at the time point of the interim analysis will be associated with major statistical uncertainties.

### Methods for additional analyses (e.g. subgroup analyses) {20b}

#### Sensitivity analyses

We will conduct a sensitivity analysis to explore whether models with more complicated correlation structures are better fits to the data. These models are not our primary analysis models as there is limited understanding of when such models will converge and how to choose between the various correlation structures that may be plausible. To this end, we will additionally fit generalised linear mixed models (with the same link functions and fixed effects described above) to include a discrete time decay correlation structure that includes a random cluster effect with an auto-regressive structure (AR [1]).

To explore whether the fixed period effect is both parsimonious and adequate for representing the extent of any underlying secular trend, we will model the time effect using a spline function. Models will also be extended to include random cluster by intervention effects (with a non-zero covariance term) to examine whether the results are sensitive to the assumption of no intervention by cluster interaction. A fully adjusted covariate analysis will adjust for a set of prespecified individual-level covariates of known prognostic importance.

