#### Patient participants

The inclusion criteria for the patient are as follows:At least 15 years of age;Trauma occurring less than 48 h before arrival at the hospital;Presenting to the emergency department of the participating hospitals, with a history of trauma defined as any of the reasons listed in the International Classification of Diseases chapter 20 as the reason for presenting;Admitted, or died between arrival at the hospital and admission, or were referred/transferred from the emergency department of a participating hospital to another hospital for admission; andManaged by a participating unit in the emergency department.

The exclusion criteria for the patient participants are as follows:Presenting with isolated closed extremity fracture;Admitted directly to a ward without being seen by a physician in the emergency department.

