## Participant timeline {13}

The patient participants will be adult trauma patients who present to the emergency departments of the participating hospitals and are admitted or transferred for admission. Participants are screened by the clinical research coordinators and all participants who meet the eligibility criteria will be included in the study. The participants’ baseline and subsequent data will be collected as per Tables 2 and 3.

**Table 2 Tab2:** Overview of trial procedures before and during patient admission

Procedures	Screening	Consenting	Initial assessment	In-hospital care
Eligibility criteria	√			
Study information^a^		√		
Informed consent^a^		√		
Baseline data collection			√	
Prehospital data collection			√	
ATLS® adherence^b^			√	
ED data collection			√	
Hospital data collection				√
Surgery data collection				√
Imaging data collection				√
Transfusion data collection				√
Injury data collection				√
Mortality data collection				√
Assessment of safety events				√

^a^Clinical research coordinators will inform patient participants about the study, including their right to withdraw their data from the study at any time, and will approach them in person or by telephone for informed consent for the collection of non-routinely recorded

^b^ATLS® adherence will be assessed by observing the care provided to a random sample of patient participants included using the nested staircase design

*Abbreviations*: *ATLS®* Advanced Trauma Life Support®, *ED* Emergency Department

**Table 3 Tab3:** Overview of trial follow-up procedures

Procedures	Within 7 days of discharge	30 days	90 days
Mortality data collection	√	√	√
EQ-5D/WHODAS	√	√	√
Return to work		√	√
End of study			√

*Abbreviations*: *EQ-5D* EuroQol 5 dimensions, *WHODAS* World Health Organization Disability Assessment Schedule

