### Methods in analysis to handle protocol non-adherence and any statistical methods to handle missing data {20c}

We will present the frequency and percentage of missing data for all variables. If the percentage of missing data for the primary outcome is less than 10%, we will perform a complete case analysis. If the percentage of missing data for the primary outcome is 10% or more, we will handle missing data depending on the missing data mechanism. If the data are missing at random (MAR), we will perform multiple imputation using multiple imputation by chained equations (MICE), imputing data for the primary outcome as well as all covariates included in the fully adjusted model. The number of imputations will be determined by the percentage of missing data, with a minimum of 20 imputations. If there is evidence that the data are missing not at random (MNAR), we will explore the impact of this assumption using a sensitivity analysis (e.g., pattern mixture models or selection models) to assess how robust our findings are to different assumptions about the missing data mechanism. Additionally, we will perform diagnostic checks after multiple imputation to ensure the quality of the imputation process, including comparing distributions of observed and imputed data and checking convergence.

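### Prognostic covariates are kept out of the primary model and used only in a sensitivity analysis, which gives up some power and partial protection against measured case-mix shift

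*Protocol article*

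**What the plan says.** The primary model is set out under Statistical methods for primary and secondary outcomes {20a}: "We will include fixed effects for period and a fixed effect for intervention exposure", with random cluster and cluster-by-period effects. No patient characteristic appears in it, and neither does cluster size, on which the constrained randomisation is balanced (Sequence generation {16a}).

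Adjustment appears under Sensitivity analyses in {20b}: "A fully adjusted covariate analysis will adjust for a set of prespecified individual-level covariates of known prognostic importance". The covariates are evidently to be in the data set, because the missing-data section {20c} plans for "imputing data for the primary outcome as well as all covariates included in the fully adjusted model". Participant timeline {13} states that "The participants’ baseline and subsequent data will be collected as per Tables 2 and 3", and Table 2 lists baseline, prehospital, emergency department and injury data as categories without naming variables.

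On the conduct side, {17a} says "It is not possible to blind trial participants or care providers in this stepped-wedge trial" and "We will not blind outcome assessors nor data analysts because of how the intervention is randomised by time". Under {16b}, "The randomisation will be concealed for as long as it is logistically possible". Site research coordinators include the patients ({16c}). One inclusion criterion is met by patients who are "Admitted, or died between arrival at the hospital and admission", or who are sent on to another hospital for admission. Interim analyses {21b} compares patient characteristics between conditions to look for differential recruitment or ascertainment.

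**The concern.** Eligibility is settled after arrival, by an admission or transfer decision in the emergency department where the trained physicians work. The course content includes triage and transfer between hospitals ({11a}), so training could plausibly change who qualifies. If it did, the mix of patients would differ between phases, and an unadjusted mortality contrast would carry that difference whole. The protocol sees this risk, but its stated response is a comparison of characteristics at the interim, which does nothing to the primary estimate.

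There is also a power argument. Covariates that predict death explain part of the outcome variation, and using them raises the chance of detecting a true effect without recruiting anyone. The article gives a reason for keeping the more complex correlation structures out of the primary model. It gives none for keeping prognostic covariates out.

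**Working it through.** **1. The plan's own figures.** Inputs from Sample size {14}, Trial design {8} and {20a}: 30 clusters in six batches of five, 12 patients per cluster-month, 13 months of which one (transition) is dropped, a 6-month overlap between batches, 20% versus 15% mortality, ICC 0.02, CAC 0.9, discrete time decay, two-sided 5%.

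Sample size: 30 × 12 × 12 = 4320, as stated.

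Power: I computed the generalised least squares variance of the exposure effect on the risk-difference scale, with categorical calendar months shared across batches, batches starting 7 months apart and equal cluster sizes. Then power = Φ(0.05/SE − 1.96). The step timings are in a figure that is not shown, so four sets of control-month counts were tried:

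| Control months by sequence | SE | Power |
|---|---|---|
| 4, 5, 6, 7, 8 | 0.01562 | 0.893 |
| 3, 5, 6, 7, 9 | 0.01567 | 0.891 |
| 3, 4, 6, 8, 9 | 0.01602 | 0.877 |
| 2, 4, 6, 8, 10 | 0.01614 | 0.872 |

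For the first row, 0.05/0.01562 − 1.96 = 1.24 and Φ(1.24) = 0.893. This is consistent with the stated power of about 90%, which does not rely on adjustment.

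**2. Gain from adjustment, risk-difference scale.** Multiply the individual-level residual variance by (1 − R²) and leave the cluster variance unchanged. R² is an assumption.

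| R² | SE ratio | Power, timing 4–8 | Power, timing 2–10 | Equivalent unadjusted N = 4320/(1 − R²) |
|---|---|---|---|---|
| 0 | 1 | 0.893 | 0.872 | 4320 |
| 0.05 | 0.983 | 0.903 | 0.883 | 4547 |
| 0.1 | 0.965 | 0.913 | 0.894 | 4800 |
| 0.2 | 0.929 | 0.931 | 0.915 | 5400 |
| 0.3 | 0.89 | 0.949 | 0.936 | 6171 |

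At ICC 0.05, the top of the protocol's range, the same two timings go from 0.765 and 0.744 (no adjustment) to 0.786 and 0.767 (R² 0.1), and to 0.832 and 0.818 (R² 0.3).

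**3. Odds-ratio scale.** The primary estimand is an odds ratio from a logit model, and step 2 does not carry over to its standard error. In a simulation of 4320 independent patients (clustering ignored), 20% versus 15%, with one normal covariate at R² of about 0.13, 0.25 and 0.35, the SE of the conditional log odds ratio rose by about 7%, 15% and 23%. The estimate moved further from the null by more than that, so z rose from about 4.3–4.4 to 4.7–5.2. Power improves, but not through a smaller SE.

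**4. Case-mix illustration, assumptions only.** Suppose training has no effect on any patient's risk, but 5 to 10% more patients are admitted, with 2% mortality. Crude mortality becomes (0.20 + 0.05 × 0.02)/1.05 = 19.1%, or (0.20 + 0.10 × 0.02)/1.10 = 18.4%. These are falls of 0.9 to 1.6 points, 17 to 33% of the 5-point target. The protocol offers no estimate of either input.

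**The case against.** The strongest reply is that both analyses are prespecified and both will be run, so the choice is only which one leads, and the trial already claims about 90% power without covariates. That is true. Nothing in the article is contradictory or miscalculated on this point.

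There are real safeguards. All eligible patients are included ({15}), consent for routine data is opt-out ({26a}), deaths before admission and transfers count as included, and the interim comparison looks for imbalance. These limit coordinator discretion. They do not stop the eligible population from changing if admission or transfer decisions change.

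Several stronger readings are tempting and should not be drawn:

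- A reader might infer that the SE of the primary odds ratio would fall. It would not (step 3).
- A reader might infer that power is really far lower and adjustment is needed to rescue it. With period effects fitted separately in each batch, the same approach gives 0.35 to 0.62 over these timings. That rests on a different model, which the article does not say it will use, and it is not evidence for this point.
- A reader might infer that adjustment would remove selection through the admission decision. It handles measured case mix only, and no calculation here shows how much of the shift in step 4 the proposed covariates would absorb.
- A reader might assume that first consciousness level and blood pressure are available and untouched by training. The article names neither. The trained physicians manage the first hour ({11a}), so the timing and completeness of such recordings could differ by phase.

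**Conclusion.** The point holds as an avoidable weakness in a choice that the article states itself, so it is not a detail left to the statistical analysis plan. The direction of the power gain is secure for covariates that predict death. Its size is not. It rests on an assumed R² and, for the power figures, on shared calendar months, equal cluster sizes and assumed step timings. Over R² of 0.1 to 0.3 the gain at ICC 0.02 is about 2 to 6 percentage points of power. A list confined to age, sex and mechanism might explain less; at R² 0.05 the gain is about 1 point. The case-mix argument is qualitative: the route is plausible and the protocol recognises the risk, but the documents do not show that a shift will occur or how large it would be.

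**What to change.** Make the primary model adjust for a short list of covariates, named before the trial statistician receives data and fixed at or before arrival: age, sex and mechanism or type of injury. Add cluster size, the balancing variable of the constrained randomisation. Include first recorded vital signs only if they are confirmed as collected and recorded independently of the trained physicians. Leave out injury findings that depend on work-up, which training may alter.

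State that the odds ratio is conditional on these covariates. Report a standardised risk difference from the same logit model, which also avoids depending on convergence of the identity-link model. Keep the unadjusted model as the sensitivity analysis.

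Amend {20c} as well. Imputation, including that of covariates, is triggered only when at least 10% of the primary outcome is missing, and {18b} expects very little to be missing. Under that rule an adjusted primary model would drop patients who lack a covariate. A missing-covariate rule that does not depend on outcome missingness is needed.

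The cost is a revision of {20a}, {20b} and {20c} and of the statistical analysis plan, a small amount of covariate imputation, and a conditional odds ratio that differs from the unadjusted one. With inclusion expected to run until about November 2029 (Trial status), there is time to do it.
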